# PROTOCOL SYNOPSIS

The primary objective of this Phase 2 clinical trial is to compare the safety and antimicrobial activity of a moxifloxacin-containing regimen (moxifloxacin, rifampin, pyrazinamide, ethambutol [MRZE]) in which moxifloxacin has been substituted for isoniazid, to the standard control regimen (isoniazid, rifampin, pyrazinamide, ethambutol [HRZE]) in the first two months of treatment of sputum smear-positive pulmonary tuberculosis. The assessment of antimicrobial activity will be sputum culture-conversion. Higher rates of sputum culture conversion after 2 months of treatment with a moxifloxacin-containing regimen would support Phase 3 clinical trials of moxifloxacin in treatment regimens of less than the current 6 month standard regimens.

The specific aims of this study are to:

Primary To compare the culture-conversion rates at the end of the intensive phase of therapy of the moxifloxacin regimen vs. that of the isoniazid regimen

Secondary To compare the safety and tolerability of the moxifloxacin regimen to that of the isoniazid regimen

To determine the time to culture-conversion of the moxifloxacin regimen and the isoniazid regimen, using data from 2-, 4-, 6-, and 8-week cultures.

To compare the proportion of patients with any Grade 3 or 4 adverse reactions

To compare adverse events and 2-month culture conversion rate among HIV-infected patients vs. HIV-uninfected patients

To compare the rates of treatment failure of the moxifloxacin regimen to the isoniazid regimen

To determine whether there is delayed toxicity attributable to moxifloxacin (toxicity that becomes evident after the 2 months of moxifloxacin therapy)

Rationale – Current treatment of smear positive pulmonary tuberculosis requires a minimum of 6 months, a treatment duration that is challenging for patients and tuberculosis control programs. Therefore, a high priority in tuberculosis research is the identification of agents that can shorten treatment. Several fluoroquinolone antibiotics have potent activity against *Mycobacterium tuberculosis* *(M. tuberculosis)* in preclinical testing. Of the currently available fluoroquinolones, moxifloxacin has excellent activity *in vitro* and in animal models of tuberculosis, a favorable pharmacokinetic profile (serum half-life of 10-12 hours), lack of problematic drug-drug interactions, no need for dosage adjustment for renal and hepatic insufficiency, and an excellent safety profile. In addition, in the murine model of tuberculosis, the substitution of moxifloxacin for isoniazid resulted in significant reductions in the time to culture conversion and the time to sterilization when compared to the standard combination rifampin, isoniazid and pyrazinamide. However, moxifloxacin has not been fully evaluated in humans for tuberculosis treatment. There is a need to assess not only the anti-tuberculosis activity of moxifloxacin-containing regimens, but also the safety of more prolonged therapy with moxifloxacin.

Two-month culture conversion rates are a well-accepted surrogate marker for the sterilizing activity of anti-tuberculosis drugs. Rifampin and pyrazinamide, the key drugs in current 6-month regimens, markedly increase 2-month culture-conversion rates. Therefore, this study will use 2-month culture conversion rate as the measure of antimicrobial activity of moxifloxacin.

# Study Design

This study will be a multicenter, placebo-controlled, double-blind trial evaluating the effect of using moxifloxacin (M) in place of isoniazid (H), in combination with rifampin (R), pyrazinamide (Z) and ethambutol (E) on 2-month culture conversion rates among patients with sputum smear-positive pulmonary tuberculosis. The protocol will enroll HIV-infected and uninfected subjects at Tuberculosis Trials Consortium (TBTC) sites. Subjects who meet the inclusion criteria will be randomized to one of the following two arms:

Intensive Phase Study Regimens

| **Study Regimen** | **Intensive phase (first 8 weeks of anti-TB therapy)** | |
| --- | --- | --- |
| Control regimen | HRZE daily* (+ moxifloxacin placebo)† |  |
| Moxifloxacin regimen | MRZE daily* (+ isoniazid placebo) † |  |

H-isoniazid; R-rifampin; Z-pyrazinamide; E-ethambutol; M-moxifloxacin

* Daily therapy will be 5 days per week. However, at the discretion of the investigator, patients in either study arm may be given therapy 7 days per week during the first two weeks of the study (only 5 doses will be counted toward completion of the four-drug intensive phase of therapy).

† Vitamin B6 (50 mg) will be given with each dose of therapy

After completion of intensive phase therapy, patients in all study arms will then be treated for 18 weeks (30 weeks for those with cavitation on initial chest radiograph plus a positive sputum culture for *M. tuberculosis* at 2 months of therapy) with an ATS/IDSA/CDC-recommended continuation phase regimen.

The moxifloxacin dose will be the currently licensed dose of 400 mg. Because cavitation at baseline (time of diagnosis) is associated with a substantially decreased rate of 2-month culture conversion (67% vs. 85% in TBTC Study 22), randomization will be stratified by presence of cavitation. In addition, randomization will be stratified by geographic continent.

# Inclusion criteria

1. Suspected pulmonary tuberculosis with acid-fast bacilli in a stained sputum smear. Patients whose sputum cultures do not grow *M. tuberculosis*, and those having an *M. tuberculosis* isolate resistant to (one or more) isoniazid, rifampin, pyrazinamide, or fluoroquinolones will be discontinued from the study, but followed for 14 days to detect late toxicities from study therapy. Patients having extra-pulmonary manifestations of tuberculosis, in addition to smear-positive pulmonary disease, are eligible for enrollment.
2. Willingness to have HIV testing performed, if HIV serostatus is not known or if the last documented negative HIV test was more than 6 months prior to enrollment
3. 7 (seven) or fewer days of multidrug therapy for tuberculosis disease in the 6 months preceding enrollment
4. 7 (seven) or fewer days of treatment with a fluoroquinolone during the 3 months preceding enrollment
5. Age > 18 years
6. Karnofsky score of at least 60 (requires occasional assistance but is able to care for most of his/her needs)
7. Signed informed consent
8. Women with child bearing potential must agree to practice an adequate (barrier) method of birth control or to abstain from heterosexual intercourse during study therapy.
9. Laboratory parameters done at, or  14 days prior to, screening:

- Serum amino aspartate transferase (AST) activity ≤ 3 times the upper limit of normal
- Serum total bilirubin level ≤ 2.5 times the upper limit of normal
- Serum creatinine level ≤ 2 times the upper limit of normal
- Complete blood count with hemoglobin level of at least 7.0 g/dL
- Complete blood count with platelet count of at least 50,000/mm3
- Serum potassium ≥ 3.5 meq/L
- Negative pregnancy test (for women of childbearing potential)

### Exclusion criteria

1. Breast-feeding
2. Known intolerance to any of the study drugs
3. Known allergy to any fluoroquinolone antibiotic
4. Concomitant disorders or conditions for which moxifloxacin, isoniazid, rifampin, pyrazinamide, or ethambutol are contraindicated. These include severe hepatic damage, acute liver disease of any cause, and acute uncontrolled gout.
5. Current or planned therapy during the intensive phase of tuberculosis treatment using drugs having unacceptable interactions with rifampin (rifabutin can be substituted for rifampin during the continuation phase of therapy)
6. Current or planned antiretroviral therapy during the intensive phase of tuberculosis treatment
7. History of prolonged QT syndrome or current or planned therapy with quinidine, procainamide, amiodarone, sotalol, disopyramide, ziprasidone, or terfenadine during the intensive phase of tuberculosis treatment.
8. Pulmonary silicosis
9. Central nervous system TB

Primary endpoints

1. The proportion of patients having a negative sputum culture at 2 months of therapy
2. The proportion of patients who discontinue assigned study therapy for any reason during the first 2 months

Study Management

Patients will have study visits every two weeks during the first 2 months of therapy. At each study visit, there will be a clinical assessment for toxicity and a sputum specimen will be obtained for smear and culture (two sputum specimens will be obtained after 8-weeks). Mycobacterial cultures must include an approved broth culture system, supplemented by at least one solid medium. Patients who are unable to produce an expectorated sputum specimen at weeks 2, 4, 6, or 8 will have sputum induction.

Specific monitoring will be performed for retinal toxicity, which is a recognized side effect of ethambutol and has been observed in some animal species after prolonged dosing of moxifloxacin (though not reported in clinical trials or post-marketing surveillance of moxifloxacin). Monitoring for retinal toxicity will consist of visual acuity and color vision testing per standard site practice. Laboratory monitoring will consist of a CBC, serum AST, bilirubin, and creatinine, and will be obtained at 2, 4, 6, 8, and 12 weeks. Because significant cardiotoxicity has not been observed among the over 10 million patients treated with moxifloxacin after its approval and is not associated with the duration of treatment in animal models, electrocardiographic monitoring will not be done during this study.

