# Table 14. Doses of study medications during the intensive phase

| **Drug** | **Dose for daily therapy** |
| --- | --- |
| Moxifloxacin | 400 mg |
| Rifampin |  |
| < 45 kg | 450 mg |
| > 45 kg | 600 mg |
| Isoniazid | 300 mg |
| Pyrazinamide |  |
| < 40 kg | 25 mg/kg rounded to nearest 500 mg* |
| 40-55 kg | 1000 mg |
| > 55 kg - 75 kg | 1500 mg |
| > 75 kg - 90 kg | 2000 mg |
| > 90 kg | 2000 mg |
| Ethambutol |  |
| < 40 kg | 15 mg/kg rounded to nearest 100 mg |
| 40-55 kg | 800 mg |
| > 55 kg - 75 kg | 1200 mg |
| > 75 kg - 90 kg | 1600 mg |
| > 90 kg | 1600 mg |

* for pyrazinamide dosing in patients < 40 kg, 1000 mg typically used instead of 500 mg

Ethambutol may be discontinued if the patient’s *M. tuberculosis* isolate is susceptible to isoniazid, rifampin, pyrazinamide, and fluoroquinolones, as demonstrated by laboratory studies.

- 1. Continuation Phase Therapy

After completing the intensive phase of therapy, patients in all study arms will then be treated with an ATS/IDSA/CDC-recommended continuation-phase regimen. Recommended continuation-phase regimens that may be used include

- isoniazid + rifampin given daily [5 days/wk], thrice-weekly, or twice-weekly
- isoniazid + rifabutin for patients on medications having unacceptable drug-drug interactions with rifampin
- isoniazid + rifapentine once-weekly for HIV-seronegative patients with non-cavitary pulmonary disease plus a negative sputum smear at 2 months
- rifampin + pyrazinamide + ethambutol for patients who are intolerant of isoniazid (note: patients with known isoniazid intolerance cannot be enrolled in the protocol, but patients may develop isoniazid intolerance during study therapy).

The total duration of therapy will be 26 weeks (6 months) except that patients who have cavitation plus a positive sputum culture at the end of the intensive phase of therapy will receive a total of 38 weeks (9 months) of therapy.

- 1. Primary Objective
- To compare the culture-conversion rate at the end of the intensive phase of therapy of the moxifloxacin regimen vs. that of the isoniazid regimen
  1. Secondary Objectives

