### To compare the safety and tolerability of the moxifloxacin regimen to that of the isoniazid regimen

### To determine the time to culture-conversion of the moxifloxacin regimen and the isoniazid regimen using data from 2-, 4-, 6-, and 8-week cultures

- To compare the proportion of patients with any Grade 3 or 4 adverse reactions
- To compare adverse events and 2-month culture conversion rates among HIV-infected patients vs. HIV-uninfected patients
- To compare the rates of treatment failure of the moxifloxacin regimen and the isoniazid regimen
- To determine whether there is delayed toxicity attributable to moxifloxacin (toxicity that becomes evident after the 8 weeks of moxifloxacin therapy)
  1. Study Endpoints

**Sputum culture conversion** – sputum culture obtained at the end of the intensive phase of therapy has no growth of *M. tuberculosis*. The end of the intensive phase of therapy will be defined by completion of the required number of directly-observed doses (as defined in Section 3.1), rather than by a specific number of weeks of therapy. In order to assure that each subject will be evaluable for the primary endpoint, two sputum cultures will be obtained at the end of the intensive phase of therapy. These two cultures must have been obtained (a) 0-7 days after the completion of the intensive phase of therapy (preferably, one on the day of completion and one within 7 days of completion), and (b) prior to receiving more than one dose of continuation phase therapy. Sputum culture conversion will be based on the results of both sputum cultures performed at the end of the intensive phase of therapy.  **Both sputum cultures, if evaluable, should be negative for *M. tuberculosis* in order to conclude that sputum culture conversion was achieved.** Sputum cultures that are overgrown by bacteria and/or yeast will be considered unevaluable. Subjects who are unable to produce a specimen for sputum culture despite an attempt with sputum induction will be considered to have had a negative culture on that date.

**Safety and tolerability endpoints** – the primary endpoint for the analysis of safety and tolerability will be the proportion of patients who discontinue the assigned study regimen for any reason. Other aspects of safety and tolerability that will be assessed as secondary endpoints include mortality, the occurrence of Grade 3 and 4 toxicities and the rate and types of toxicity thought related to study drug by the investigator.

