Study entry is open to male and female patients and patients of all ethnic backgrounds.  Historically, the majority of patients with tuberculosis at clinical sites are males.  The gender, ethnic and socioeconomic background of the subjects recruited for this study is expected to mirror that of the population the hospitals and clinics served, and that of the population most affected by tuberculosis. Pregnant or breast-feeding women and children will not be enrolled because of uncertainties about the safety of moxifloxacin in those groups of patients.  Subjects will be enrolled if they meet all of the following inclusion criteria and none of the exclusion criteria:

- - 1. Inclusion Criteria

1. Suspected pulmonary tuberculosis with acid-fast bacilli in a stained smear of expectorated or induced sputum. Patients whose sputum cultures do not grow *M. tuberculosis* and those having an *M. tuberculosis* isolate resistant to (one or more) isoniazid, rifampin, pyrazinamide, or fluoroquinolones will be discontinued from the study, but followed for 14 days to detect late toxicities from study therapy. Patients having extra-pulmonary manifestations of tuberculosis, in addition to smear-positive pulmonary disease, are eligible for enrollment. Sputum must be expectorated or induced; smear results from respiratory secretions obtained by bronchoalveolar lavage or bronchial wash may not be used for assessment of study eligibility.
2. Willingness to have HIV testing performed, if HIV serostatus is not known or if the last documented negative HIV test was more than 6 months prior to enrollment. HIV testing does not need to be repeated if there is written documentation of a positive test (positive ELISA and Western Blot or a plasma HIV-RNA level greater than 5000 copies/ml) at any time in the past
3. 7 (seven) or fewer days of multidrug therapy for tuberculosis disease in the 6 months preceding enrollment
4. 7 (seven) or fewer days of fluoroquinolone therapy in the 3 months preceding enrollment
5. Age > 18 years
6. Karnofsky score of at least 60 (requires occasional assistance but is able to care for most of his/her needs; see Appendix B)
7. Signed informed consent
8. Women with child-bearing potential must agree to practice an adequate (barrier) method of birth control or to abstain from heterosexual intercourse during study therapy.
9. Laboratory parameters done at, or  14 days prior to, screening:

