All baseline isolates of *Mycobacterium tuberculosis* will undergo drug susceptibility testing at the site’s local laboratory. The baseline isolate will be defined as the first *M. tuberculosis* isolate obtained from a sputum culture; in some instances this sputum specimen may have been obtained prior to study screening. An *M. tuberculosis* isolate cultured in a laboratory other than a site’s study laboratory of record may be designated as the baseline isolate if the isolate is sent to the study laboratory of record. Drug susceptibility testing will include susceptibility to isoniazid, rifampin, and ethambutol. Initial susceptibility testing generally requires 4-8 weeks to complete (initial isolation followed by susceptibility testing). It is expected that patients will be enrolled in this protocol with drug-resistant isolates, most often resistance to isoniazid, with or without streptomycin resistance[109, 110]. Rifampin resistance and multidrug-resistance (resistance to isoniazid and rifampin) is uncommon among previously untreated patients in the United States[109], Uganda[110], Canada[111], and South Africa[112]. All isolates will be sent to the CDC Mycobacteriology Laboratory for confirmatory susceptibility testing; this testing will include all drugs currently used to treat tuberculosis, including pyrazinamide and fluoroquinolones. The confirmatory testing will take several additional months, and these results are unlikely to be available during the first 2 months of TB treatment. All study regimens should be highly active for isolates with susceptibility to isoniazid and rifampin.

- 1. Management of patients with baseline drug-resistant isolates

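### The discontinuation endpoint counts stops that the protocol itself orders for baseline microbiology, which dilutes it as a tolerability measure; its status and time window also differ between sections

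*Protocol*

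**What the plan says.** **Endpoint.** The Synopsis (Primary endpoints) names two primaries: a negative culture at 2 months and "The proportion of patients who discontinue assigned study therapy for any reason during the first 2 months". Section 3.5 (Study Endpoints) makes "the proportion of patients who discontinue the assigned study regimen for any reason" the primary endpoint of the safety and tolerability analysis. It gives no time limit. Mortality, Grade 3 and 4 toxicity and investigator-attributed toxicity are listed there as secondary.

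**Mandated stops.** Under the first inclusion criterion (Synopsis and Section 3.8.1), patients with no growth of M. tuberculosis, and those with an isolate resistant to one or more of "isoniazid, rifampin, pyrazinamide, or fluoroquinolones will be discontinued from the study". Section 5.2 repeats the removal from the assigned regimen for each type of resistance and foresees it in the continuation phase as well.

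**Frequency and timing.** The Background (INH resistance) puts isoniazid resistance at 5-10% in previously untreated patients. Section 5.1 states: "Initial susceptibility testing generally requires 4-8 weeks to complete". It expects confirmatory results, which include pyrazinamide and fluoroquinolones, mostly after the first 2 months.

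**Analysis sets.** Section 6.1 removes patients with resistant isolates from the culture-conversion analysis and keeps all randomised patients in the toxicity analyses. Nothing takes microbiology stops out of the discontinuation count.

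**Status.** The Synopsis lists "To compare the safety and tolerability of the moxifloxacin regimen to that of the isoniazid regimen" as a secondary aim. Section 3.3 has one primary objective, "To compare the culture-conversion rate at the end of the intensive phase of therapy of the moxifloxacin regimen" against the isoniazid regimen. Section 4.1 (end-of-intensive-phase visit) treats culture conversion as the trial's one primary endpoint.

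**The concern.** A baseline isolate is fixed before the first dose, so a stop that follows from it carries no information on how well the regimen is tolerated. The protocol deals with this for efficacy by excluding the patients. For tolerability it leaves these stops in, as events common to both arms. That pulls the risk ratio toward 1 and adds variance, which is an unhelpful direction of error for a safety comparison.

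The status and window matter too. An analyst cannot tell whether discontinuation is a primary endpoint of the trial or only of the safety analysis. The window changes the count: the intensive phase is measured in doses and may run to 70 days (Section 3.1), and stops prompted by late confirmatory results fall outside the Synopsis definition but inside that of Section 3.5.

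**Working it through.** **1. The plan's own figure.** Section 3.7 sizes the trial for culture conversion only: 75% vs 88%, two-sided 0.05, 80% power.
- Pooled two-proportion formula: [1.96·√(2·0.815·0.185) + 0.8416·√(0.1875 + 0.1056)]² / 0.13² = 138.9, so 139.
- With continuity correction: (138.9/4)·[1 + √(1 + 4/(138.9·0.13))]² = 153.9, so 154, as stated.
- 154/0.75 = 205.3, and the protocol takes 205 per arm. No power is stated for discontinuation.

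**2. Model.** Let m be the fraction stopped for baseline microbiology inside the window, equal in both arms, and p the rate of all other stops. Taking the two as independent and counting each patient once:
- observed rate = m + (1−m)p
- observed risk difference = (1−m)(p₂ − p₁)
- power = Φ[(d − 1.96·se₀)/se₁], where a and b are the observed rates, d is their difference and p̄ their mean, se₀ = √(2p̄(1−p̄)/205) and se₁ = √([a(1−a) + b(1−b)]/205), without continuity correction.

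**3. Illustration: p = 5% vs 12% (assumed; not in the protocol), 205 per arm.**

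| m | Observed rates | Risk difference (points) | Risk ratio | Power |
|---|---|---|---|---|
| 0 | 5.0% vs 12.0% | 7.0 | 2.40 | 72.1% |
| 2.5% | 7.4% vs 14.2% | 6.8 | 1.93 | 60.6% |
| 5% | 9.75% vs 16.4% | 6.65 | 1.68 | 51.5% |
| 10% | 14.5% vs 20.8% | 6.3 | 1.43 | 38.7% |

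At m = 5%: d = 0.0665, p̄ = 0.13075, se₀ = 0.03330, se₁ = 0.03314, so Φ(0.037) = 51.5%.

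**4. A second scenario.** The only discontinuation rates in the protocol are in Table 6 (another trial, levofloxacin added, 87 per arm): 11.5% vs 8.1%. Take 11.5% as the control rate and assume a 10-point excess (11.5% vs 21.5%). For m = 0, 2.5%, 5% and 10%, power is 78%, 72%, 66% and 56%. The risk ratio is 1.87, 1.71, 1.60 and 1.44, and the risk difference 10.0, 9.75, 9.5 and 9.0 points. With m at 5-10%, there would be 205·0.05 = 10 to 205·0.10 = 21 mandated stops per arm, or 0.05/0.159 = 31% to 0.10/0.2035 = 49% of control-arm events. For Table 6's own contrast, power is 21% at m = 0 and 15% and 12% at m = 5% and 10%.

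**5. How large m may be.** If every isoniazid-resistant patient stopped inside 2 months, that component would be 5-10%. With local results at 4-8 weeks, only some will. No-growth stops add an amount that the protocol does not give.

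**6. Effect of not counting microbiology stops, all randomised kept.** The observed rate lies between (1−m)p and p, because toxicity stops that precede a resistance result still count. At the lower limit with m = 10%, the 5% vs 12% case becomes 4.5% vs 10.8%: risk ratio 2.40, power 67%. Dropping ineligible isolates (205·0.9 = 184.5 per arm) gives about 67.5%, so excluding patients buys almost nothing.

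**The case against.** **All-cause discontinuation is a legitimate measure.** It avoids judging cause, and toxicity attributed to study drug is already a separate endpoint. That stands as a reason to keep the all-reason version in view. It does not justify counting a stop whose cause is a baseline laboratory result and needs no causal judgement.

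**The tolerability signal is not buried.** A reader might infer that a less tolerable regimen would pass unnoticed. The documents do not support that. Resistance and no growth precede randomisation and the trial is double-blind, so these stops should be balanced. The risk difference loses only the fraction m of itself. Mortality, Grade 3/4 toxicity and drug-related toxicity are assessed directly.

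**The size is not a forecast.** The 5% and 12% are assumptions, 10% is the top of the range for isoniazid stops inside 2 months, and the protocol promises no power for this endpoint. All of that stands.

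**The labels are partly reconcilable.** The opening sentence of the Synopsis joins safety with antimicrobial activity in the primary objective, which fits two primaries. Section 3.5 already uses a safety-only label. The window is stated once and omitted once, not contradicted outright, and Table 13 ties the study regimens to the intensive phase. Even so, the Synopsis differs from its own list of aims and from Sections 3.3 and 4.1, and the continuation-phase stops in Section 5.2 leave the window open.

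**A statistical analysis plan could split stops by reason.** It could, but the any-reason wording is fixed in the protocol, and leaving these stops out of the main count would depart from it.

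**Conclusion.** The point holds as dilution plus misaligned status and window. Followed as written, the main tolerability measure includes events unrelated to the drugs. In the assumed 5% vs 12% case, power falls from about 72% to 61%, 51.5% or 39% at m = 2.5%, 5% or 10%, and the risk ratio from 2.4 to as low as 1.4. The risk difference falls by no more than a tenth over that range. These sizes rest on assumed stop rates, on balance between arms and on an uncertain m. The wording and the label and window differences rest on the text alone. It is worth correcting because the repair costs little, but it does not threaten the culture-conversion comparison.

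**What to change.** In the Synopsis and Section 3.5, define the primary safety and tolerability endpoint as discontinuation of the assigned regimen during the intensive phase for any reason other than a baseline microbiology result (no M. tuberculosis growth, or a resistant baseline isolate).

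- Keep all randomised patients in the denominator, in line with Section 6.1. A toxicity stop that precedes a resistance result then still counts.
- State that stops for drug intolerance count as events. Section 5.2 groups rifampin and pyrazinamide intolerance with resistance, so the two need separating.
- Report microbiology stops separately by arm. Show the all-reason version and a version limited to eligible isolates as sensitivity analyses. The latter should not be the main analysis, because it discards real toxicity stops in patients later found resistant.
- Use one window and one label throughout, with culture conversion as the single primary efficacy endpoint, and align the Synopsis aims, Section 3.3 and Section 4.1.

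The cost is wording in those sections and one classification of each stop by reason, which should be finished before unblinding. Section 5.4 already requires study drug discontinuations to be reported on the Adverse Event Form, and the baseline culture and susceptibility results are collected anyway.
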